## Discussion

Although acupuncture treatment has been administrated for thousands of years, the crucial components of acupuncture remain unclear [33]. This study is a double-blind, randomised, placebo-controlled trial to evaluate the efficacy of acupuncture in treating functional neck/shoulder stiffness. Besides genuine acupuncture (which includes both genuine needle penetration and accompanying ritual of acupuncture), the study utilizes two types of double-blind placebos: skin-touch placebo (which includes the ritual) and no-touch placebo needles (the ritual of acupuncture alone). To clarify the relationship between the cause and the result with minimum bias as possible, we will evaluate the efficacy of acupuncture immediately and 24 hours after treatment. The results will provide high-quality evidence of the efficacy of acupuncture treatment for functional neck/shoulder stiffness with few confounding factors.

Furthermore, we will conduct subgroup analyses on practitioners’ or patients’ guesses in addition to intention-to-treat analysis to understand and discuss the efficacy of needle application, the efficacy of recognition of treatment type, and the relationship between the efficacy of needle application and the efficacy of treatment recognition, by which the efficacy and effectiveness of acupuncture treatment *per se* can be determined. These analyses could provide information on the crucial component of acupuncture such as skin penetration, skin pressure, performance of acupuncture ritual itself as well as the influence of psychological factors between mind of patients and practitioner [33]. Further we will discuss importance of de-qi to produce effect of acupuncture treatment. Thus, the value of acupuncture treatment will be discussed from multiple perspectives and give us new insight that will enable us to implement acupuncture in clinical practice. In addition to improving neck/shoulder stiffness, a critical discussion will be given regarding practitioner and patient blinding and the limitations of the study which is to see short term effect, not a long term follow up.

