**Discussion:**

In addition to intention-to-treat analysis, we will conduct subgroup analysis based on practitioners’ or patients’ guesses to discuss the efficacy and effectiveness of treatments with skin piercing and various placebo controls. The results of practitioner and patient blinding will be discussed. We believe this study will further distinguish the role of different components of acupuncture.

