### Patients’ evaluation immediately after treatment

The patients rate the intensity of stiffness at the area of strongest stiffness immediately after the treatment by a VRS (none, weak, moderate, strong, very strong) and on a 100 mm VAS ranging from 0 (no neck/shoulder stiffness) to 100 (most severe neck/shoulder stiffness imaginable). Also the patients rate the change in stiffness in the area of strongest stiffness compare with before the treatment by a VRS (clearly worsen, slightly worsen, no changed, slightly improved, clearly improved). When they rate “clearly or slightly worsen”, they rate the change on a 100 mm VAS ranging from −100 (worsened to the most severe stiffness imaginable) to 0 (no change). When they rate “clearly or slightly improved”, they rated the change on a 100 mm VAS ranging from 0 (no change) to 100 (completely cured no stiffness). For the no-treatment control group, after the 10 min of no-treatment period the patients report the same items.

Excluding no-treatment control group, the patients report what they feel during the treatment. If they feel pain from the treatment, they rate pain intensity on a 100 mm VAS ranging from 0 (no pain) to 100 (most severe pain imaginable). If they feel de-qi from the treatment, they rate de-qi intensity on a 100 mm VAS ranging from 0 (no de-qi) to 100 (strongest de-qi imaginable). Further they rate their pleasantness or unpleasantness to the treatment on a 200 mm VAS ranging from −100 (very unpleasant) to 0 (neither pleasant nor unpleasant) to 100 (very pleasant), and rate their satisfaction with the treatment on a 200 mm VAS ranging from −100 (completely unsatisfied) to 0 (neither satisfied nor unsatisfied) to 100 (completely satisfied).

Then, the patients guess whether the treatment is “penetrating”, “skin-touch” or “no-touch” or to record “cannot identify the treatment” and they report their confidence level in their guesses by a VRS (with confidence, with slight confidence, with little confidence, with no confidence) and on a 100 mm VAS ranging from 0 (no confidence) to 100 (full assurance) [24,28,29].

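### Guess-defined subgroups are given the task of determining efficacy, but the guesses follow the outcome rating and are not protected by randomisation

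*Protocol article*

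**What the plan says.** The Discussion states: "we will conduct subgroup analyses on practitioners’ or patients’ guesses in addition to intention-to-treat analysis". The listed purposes are the efficacy of needling, the efficacy of recognising the treatment, and "the relationship between the efficacy of needle application and the efficacy of treatment recognition, by which the efficacy and effectiveness of acupuncture treatment" itself, the sentence ends, can be determined. The next sentence adds that these analyses could inform which component of acupuncture is crucial. The abstract describes the same plan more mildly, as "subgroup analysis based on practitioners’ or patients’ guesses to discuss the efficacy and effectiveness of treatments with skin piercing and various placebo controls".

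The Methods fix when the guesses are made. In the section on evaluation immediately after treatment, patients rate stiffness, change in stiffness, pain, de-qi, pleasantness and satisfaction. After all of these comes the step that begins "Then, the patients guess whether the treatment is". The 24-hour section again lists the guess after the stiffness ratings. Practitioners guess once the four-needle treatment is complete and record clues such as the patient's expression, behaviour, bleeding and reactions to insertion or removal. Guesses, pain and de-qi are listed as secondary outcomes.

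The Statistical analysis section regresses score change on treatment mode and compares responders between needle groups. It does not name the guess as a term.

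**The concern.** A guess made after treatment is a post-randomisation variable. Patients who guess penetrating and patients who do not were not formed by the random numbers, so they may differ in outcome for reasons unrelated to needle or belief. All participants have had acupuncture and de-qi before (inclusion criterion 3). A patient who has just recorded clear relief could reasonably infer a real needle. The difference between guess groups would then run partly from outcome to guess, and reading it as an effect of recognition reverses the direction.

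Comparing needles within one guess has a related problem. If both the needle and the relief push the guess, patients who reach the same guess in different arms are selected differently on outcome.

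At stake is the interpretation of components, which is why the trial has two placebos. A recognition effect produced by selection could be reported as a finding on how acupuncture works, on the strength of a sentence saying that efficacy can be determined this way.

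**Working it through.** **Figures in the plan.** The article gives no SD, effect size or significance level for these analyses, so there is no figure to reproduce. The design numbers agree: 6 acupuncturists × 50 patients = 300 = 3 needle arms × 100 sets.

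**Order of events, from the Methods.** Randomise → treat → practitioner guesses; patient rates stiffness and change → patient guesses → 24-hour rating → second patient guess. Each patient guess follows a stiffness rating. The first guess precedes the 24-hour outcome.

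**Null model.** There are three needle arms of 100. Improvement is N(15, 20) mm in every arm, so the true needle and recognition effects are both zero. The four guess options are collapsed to penetrating or not:

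logit P(guess penetrating) = b_out × z + b_arm × a,

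where z is improvement in SD units and a = +1 (penetrating), 0 (skin-touch), −1 (no-touch). The mean, SD, both coefficients and a two-sided 0.05 level are assumptions. There were 4,000 replicates for each of 16 combinations: b_out 0, 0.25, 0.5, 1 with b_arm 0, 0.5, 1, 2.

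**Formula for the artefact.** In an arm, let P = E[p(z)] and M = E[z·p(z)]. Mean z is M/P among those guessing penetrating and −M/(1−P) among the rest. For b_out = 0.5 and b_arm = 0, P = 0.5 and M = 0.118. The gap is 0.118/0.5 + 0.118/0.5 = 0.472 SD, or 0.472 × 20 = 9.4 mm (simulated: 9.5 mm).

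**Guessed penetrating versus not (true difference 0), over the four values of b_arm:**

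| b_out | Apparent effect, mm | In SD (÷ 20) | Rejections at 0.05 |
|---|---|---|---|
| 0 | about 0 | 0 | about 5% |
| 0.25 | 3.1 to 4.9 | 0.16 to 0.25 | 27% to 56% |
| 0.5 | 6.0 to 9.5 | 0.30 to 0.48 | 76% to 99% |
| 1 | 11.7 to 16.5 | 0.59 to 0.83 | 100% |

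**Penetrating versus no-touch among those guessing penetrating.**
- b_out = 0 or b_arm = 0: no bias, rejection about 5%.
- Both non-zero: bias of −1.2 to −12.1 mm, rejection 6% to 62%, always against the penetrating needle.

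**As-randomised comparison, penetrating versus no-touch.** Rejection was 4.6% to 5.7% in all 16 scenarios.

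**Second model as a check.** Two arms, logit P = −0.5 + b·z + c·arm (arm 1 or 0), solved by numerical integration. For b from 0.4 to 1.2 and c from 0.5 to 1.5, the recognition artefact is 0.34 to 0.93 SD and the within-guess bias is −0.05 to −0.27 SD. At b = 0.25 the artefact is 0.22 to 0.24 SD, and at b = 0 it is zero.

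**The case against.** The best defence is that these analyses are additional. The primary aims are arm comparisons, the regression is on treatment mode, and the guess enters neither that model nor the responder test. The closing clause could be read as covering the whole programme, intention-to-treat included, and the abstract says only that efficacy will be discussed. How subgroups are modelled and labelled normally belongs in an analysis plan, which is not shown. Most of this stands: the primary comparison is sound and the missing label alone would be no finding. The published claim about what the analyses can determine remains, and it comes with no caution.

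A reader might infer several stronger points that the documents do not support:

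- **That the guesses are caused by the outcome.** No section says so. It is plausible for patients. It is weaker for practitioners, who leave the booth before answering, are not said to see the ratings, and whose listed clues omit stiffness relief. For the first patient guess against the 24-hour outcome, direct reverse causation is impossible, though shared causes are not.
- **That these analyses always show effects where none exist.** There is no artefact without a link between outcome and guess, and no within-guess bias unless the guess depends on both arm and outcome.
- **That the headline result is compromised.** The randomised contrasts keep their error rate whatever drives the guess.
- **That patients will be split by de-qi felt.** The text says only "Further we will discuss importance of de-qi to produce effect of acupuncture treatment"; no such split is specified.

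The link strengths and the 20 mm SD are not from the article, so the sizes are illustrations.

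**Conclusion.** The point holds at moderate severity. The Discussion gives guess-defined subgroups a part in determining efficacy and effectiveness that post-randomisation groups cannot carry. If relief influences the guess even mildly, the recognition contrast departs from zero under a true null by an amount that 300 treated patients would often declare significant. Within-guess needle contrasts can meanwhile be biased against penetration. This rests on an assumed logistic link, a binary guess and, for the millimetre values, an SD of 20 mm. The qualitative conclusion needs only that guess and outcome are linked other than through an effect of belief on outcome. It does not reach the primary intention-to-treat analysis.

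**What to change.** In the Discussion, and in the matching sentence of the abstract:

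1. State that conclusions on efficacy and on the components of acupuncture rest on the contrasts between arms as randomised.
2. Use the guesses to assess blinding, through an arm-by-guess table or a blinding index per arm.
3. Label outcome-by-guess results exploratory and non-causal. Do the same for any outcome-by-de-qi results, if they are produced.
4. Remove the claim that efficacy and effectiveness can be determined from the guess-based analyses.

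The cost is wording. Data collection, sample size and the primary analysis do not change, and the tables can still be shown. The sponsor gives up one claim that the design cannot support.
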